## 5 PARTICIPANTS AND GROUP ALLOCATION

### 5.1 Recruitment

The study will be announced to possible participants and health professionals using different media channels. Additionally, participants can be recruited by self-referral via the German Apple App store (Apple Inc.) and Google Play Store. The recruitment of 346 patients within 6 months seems feasible, because in the last app study by the study group around 350 participants were recruited within 10 months only through the German Apple App store without applying other recruitment approaches. Additionally, this study will also recruit Android users. To support faster recruitment a fee of 80 Euro will be provided to study participants for a 12-week documentation within the app.

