## 3 STUDY DESIGN

This is a two-armed, open-label, parallel-group, randomized study. Patients will be randomly allocated to one of two groups (intervention or control as a waiting list) in a 1:1 ratio (stratified for episodic and chronic migraine) to gain access either to the intervention (M-sense Migräne app) or an app version with only data input features (control app). For motivational reasons the control group participants will automatically gain access to the M-sense Migräne app after 12 weeks. These additional data and the 24-weeks follow-up in the intervention group that uses M-sense Migräne from the beginning will not be part of the DiGA study.

Methodological considerations: When planning the trial and the data analyses we were aware that the patients cannot be blinded to the group they are allocated to, which might introduce bias. However, because of the type of intervention blinding is not possible and open-label trials are common in behavioral interventions. Nevertheless, the physician classifying the headache attacks and the statistician performing the analysis will be blinded for the group allocation of the patients.

Because the number of migraine days is higher in patients with chronic migraine than in patients with episodic migraine, we use the specification of diagnosis as stratification variable during the randomization.

To reduce missing data for the primary outcome, patients are reminded within the app to complete the daily headache question and document their headaches thoroughly. Furthermore, we motivate

those patients who are non-adherent and stop the intervention to at least document their headaches within the app. Based on this we can distinguish in the group using M-sense Migräne between study dropouts and intervention dropouts (see 10.4.).

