To support a complete documentation technically, a daily headache question with a dichotomous value (headache yes/ no) has been implemented in both app versions (M-sense Migräne app and control app). This question will be shown every day when the app is opened for the first time. The app also motivates patients to open the app daily and document their headache attacks. The headache diary records the time period of attacks, as well as the pain characteristics and attendant symptoms for every documented headache attack. The choice of the primary outcome was requested by the regulatory body (BfArM) based on the Guidelines of the International Headache

Society for controlled trials on preventive (pharmacological) treatment of episodic migraine and preventive treatment of chronic migraine in adults.

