### 6.3 FURTHER MEASUREMENTS

- Adherence to the study intervention is only observed in the M-sense Migräne app group and on weekly basis. Being adherent is defined for a patient as using an app feature which is not implemented in the control app, at least one time per week.
- Tracked usage of app features during the 12 weeks is only measured in the intervention group with M-sense Migräne including (a) Headache reporting and attack classification diary; b) Medication intake diary; c) Trigger factors diary; d) Analysis function and physician report; e) Personalized education on disease- and trigger management; f) Relaxation therapy; g) Training module; h) Acute pain therapy. This data will be displayed descriptively.
- Concomitant activities/ activities are documented in both groups (activities recorded in an app diary: mindfulness practice, breathing meditation, autogenic training, muscle relaxation, qigong/tai chi, yoga, nordic walking, cardio-training, fitness course, running, cycling, and swimming) used against headache during the first 12 weeks (activity, and time spent for respective activity). Some of these activities are recommended in the app, others not. We will calculate the number of patients with respective activities.

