### 10.4.2 Dropouts in the control group

Dropouts in the control group (randomized to the control app) can only be study dropouts, because the control app does not include interventions.

Study dropouts are defined as patients who decline further participation OR are **not** answering the daily headache question at least 3 days per week at least 4 weeks consecutively. For this group missing data will be imputed based on data from the control group using reference-based multiple imputations, assuming missing at random (MAR).

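### The added effort to keep patients documenting can reach only the app arm as written, an avoidable risk of unequal missing primary-endpoint data in a direction the documents do not settle

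*Combined protocol and SAP*

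**What the plan says.** SAP 3 sets out two layers of effort against missing primary-outcome data. The first has no arm restriction: "patients are reminded within the app to complete the daily headache question and document their headaches thoroughly". The second is additional and is aimed at "those patients who are non-adherent and stop the intervention to at least document their headaches within the app". The SAP does not say who makes this contact, when, by what channel or how often.

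Other sections determine who can belong to the second group. SAP 6.3 states: "Adherence to the study intervention is only observed in the M-sense Migräne app group and on weekly basis". It defines being adherent as "using an app feature which is not implemented in the control app, at least one time per week". SAP 10.4.2 says that dropouts in the control group "can only be study dropouts, because the control app does not include interventions".

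Several measures are not limited to one arm. The daily headache question is in both app versions (SAP 6.1), and the same paragraph adds: "The app also motivates patients to open the app daily and document their headache attacks". Protocol 5.1 says that "a fee of 80 Euro will be provided to study participants for a 12-week documentation within the app". Controls also receive the full app after 12 weeks, which protocol 4.1 presents partly as motivation to supply data until then.

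**The concern.** In an open-label trial with a patient-reported diary endpoint, the effort made to obtain that endpoint should not depend on the arm. Here one part of it does. An app-arm patient who stops the intervention is urged to continue the diary. A control whose diary lapses in the same way has no corresponding step in the plan.

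Three features give this some weight. The sample size has no allowance for dropout and relies on imputation (SAP 7). Study dropouts are imputed by different rules in the two arms: copy increments in reference for the app arm (10.4.1), missing at random within the control arm (10.4.2). A change in who becomes a study dropout therefore also changes which assumption carries the estimate. Finally, SAP Table 2 compares study dropouts between groups with a chi-square test. Study dropout is defined largely by not answering the daily question, which is the behaviour the extra effort is meant to change.

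**Working it through.** **Step 1: who can receive the second effort.** It is given to patients who are non-adherent and stop the intervention (SAP 3). Non-adherence means a week without use of a feature that the control app lacks, and it is recorded in the app arm only (6.3). Controls have no intervention to stop (10.4.2). As written, the second effort is confined to the app arm. The difference in effort follows from the text alone. A difference in missing data does not, and depends on how well the effort works and on how many patients would have lapsed in each arm without it.

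**Step 2: the planning figure.** Inputs from SAP 7: difference 1.27 days, SD 4.20, two-sided alpha 0.05, power 80%. The exact two-sample t-test gives power 0.7985 at 172 per group and 0.8008 at 173, so the stated 173 per group is reproduced. It assumes complete or fully imputed data.

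**Step 3: size of a possible shift.** The documents give no missing-data rate for either arm, so these inputs are assumptions:

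- missing share in controls, m_c = 15%;
- missing share in the app arm, m_a = 7.5%, 12% or 13.5%, for a strong, modest or weak effect of the extra contact;
- D = 1 to 4 days, the amount by which patients who stop documenting differ from what is imputed for them, taken as equal in both arms.

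If the true values of these patients exceed the imputed values by D, the control mean is too low by m_c × D and the app mean by m_a × D. The estimated difference (control minus app) then moves by −(m_c − m_a) × D. In absolute size:

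| m_a | m_c − m_a | D = 1 | D = 4 | share of 1.27 |
|---|---|---|---|---|
| 7.5% | 0.075 | 0.075 | 0.30 | 6% to 24% |
| 12% | 0.030 | 0.030 | 0.12 | 2% to 9% |
| 13.5% | 0.015 | 0.015 | 0.06 | 1% to 5% |

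**Step 4: direction.** With fewer missing in the app arm, the effect is understated if patients who stop do worse than imputed and overstated if they do better. Both signs reverse if the app arm has more missing data. The documents settle neither question.

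**Step 5: the dropout comparison in Table 2.** At 7.5% and 15% of 173 the expected counts are about 13 and 26. The uncorrected chi-square test on 13/173 versus 26/173 gives p = 0.027. Over repeated trials with 173 per arm, the test would be significant in about 61% at 7.5% versus 15%, 13% at 12% versus 15%, and 7% at 13.5% versus 15%, against a nominal 5%. The result depends almost entirely on the assumed effect of the extra contact.

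**The case against.** The strongest reply is that missing data need not differ at all. App-arm patients have a route to disengagement that controls lack: they can tire of an intervention and abandon the app with it. The SAP 3 effort addresses that route, and continuing to collect outcomes after treatment stops is sound practice. It may narrow a gap that would otherwise exist. This stands, and it is why the direction is left open.

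A reader might infer that a control with a fading diary gets one general reminder and nothing else. The documents do not support that. The daily question, the in-app motivation to document and the 80 Euro fee are not arm-specific, and later access to the full app is a retention incentive of the controls' own. However, none of these is a response to a patient who has stopped documenting, and nothing shows that they balance the added contact.

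It can also be said that the SAP specifies no trigger or channel, so the contact may be no more than information given when a patient stops. Protocol 5.5 allows any participant to give up the intervention and still complete questionnaires. That is fair, but it is a further reason to describe the procedure.

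Equal missing shares would not guarantee that bias cancels, because the two imputation rules can produce a different D in each arm. This too is correct: the fix removes one avoidable source of imbalance and does not make the missing data harmless. The common weekly missing-data rule, the alternative imputation and the FAS analysis (SAP 10.4.3, 10.4.1 and 10.5.2) help to reveal or probe a problem but do not equalise the effort.

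**Conclusion.** The point holds as a risk. One part of the follow-up effort is arm-specific as the SAP is written, and no equivalent is described for controls. It is tempting to go further and say that missing primary-endpoint data will differ between arms by design. The documents do not support that: they give no rates, most retention measures are shared, and the extra effort could widen or narrow a gap.

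Under the assumed rates the shift is about 0.015 to 0.30 days, or roughly 1% to 24% of the planned 1.27 days. The upper end needs both a halving of missing data by the extra contact and a 4-day discrepancy. The Table 2 comparison of study dropouts could also partly reflect unequal contact, but that test is exploratory, and the 61% figure should not be cited apart from the halving assumption that produces it. This is a cheap improvement worth making, not a flaw that undermines the primary analysis.

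**What to change.** In SAP 3 and in the app configuration, add a documentation prompt triggered identically in both arms by the rule already in SAP 10.4.3: the daily headache question answered on fewer than 3 days in a study week. Specify the same wording, channel and maximum number of contacts for both arms. Report the number of prompts sent and the number of missing diary weeks by arm.

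The existing contact with app-arm patients who stop the intervention may stay, since removing it would give up a chance to keep those patients documenting. SAP 3 should state who makes that contact, when and how, so that a reader can judge what asymmetry remains.

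The cost is a notification setting, a few sentences in the SAP and a few more messages to patients.

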## 4 INTERVENTION AND CONTROL

The intervention group receives the M-sense Migräne app in the DiGA study for 12 weeks. The app includes the following features: a) Headache reporting and attack classification diary; b) Medication intake diary; c) Trigger factors diary; d) Analysis function and physician report; e) Personalized education on disease- and trigger management; f) Relaxation therapy; g) Training module; h) Acute pain therapy, and i) Behavioral Change Techniques.

The control group will use within the 12 weeks an app (“control app”) that only includes data input features (headache reporting and diary and medication intake diary) and questionnaires. The headache diary will not show any attack classification, analysis or aggregated reports on the documented data to the patient. The headache diary is limited to the last seven days, which means that patients cannot enter or edit headache attacks or medication intakes that date back seven days or longer. The control app does not contain any of the other abovementioned app interventions.

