### 4.2 Justification of study design and approach

The study takes into account the current guidelines of the International Headache Society for controlled trials on preventive pharmacological treatment of episodic migraine and preventive treatment of chronic migraine in adults. We decided to perform a randomized controlled trial to reduce the confounding of results as much as possible. Because of the type of intervention used within the study

blinding of participants is not possible. Nevertheless, the physician classifying the headache attacks and the statistician performing the analysis will be blinded for the group allocation of the patients. To assure high relevance of the study results to patients, a patient reported outcome (PRO) was used as primary endpoint. We decided to document all outcomes within the app in both groups to reduce the bias that different types of documentation in intervention and control group might introduce to the data.

Although we assess most of the relevant diagnostic criteria within the app we decided to have the verification of the diagnoses by a physician. To stay within the digital framework of the study approach and taking into account possible restrictions because of the new corona virus SARS-CoV-2 this is planned as video consultation.

The DiGA study is planned for 12 weeks per patient (until primary endpoint), to gather further data and to allow the control group to receive the M-sense Migräne app after 12 weeks, a 12 week follow-up study will be added to the DiGA study.

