**Figure 2. Screenshots of the study app**

a) The comprehensive **headache diary** allows a real time tracking of headache occurrences, including headache characteristics, attendant symptoms and experienced pain intensity levels. These headache entries are automatically classified by the M-sense headache classification algorithm, a digitalized version of the ICHD-3-based headache classification. The algorithm allocates single headache attacks to the phenotypes migraine, tension-type headache (TTH), and unclassified headaches. The validity of M-sense's algorithm was assessed by comparing the classification of single headache attacks performed by the algorithm to the attack classification performed by a certified neurologist specialised in headache medicine. The substantial level of agreement between the neurologist and the algorithm was obtained (unweighted kappa=0.74). Most cases of disagreement were due to inadvertent mistakes of the neurologist as identified in the disagreement validity assessment.

b) The **diary for medication intake** allows users to track intake of their prophylactic and acute pain medication and to receive information on proper intake of medications and the potential hazards of medication overuse.

- c) The **diary for trigger factors** list potential migraine trigger factors, e.g. sleep duration, period, alcohol consumption, stress (for details see Wöber & Wöber-Bingöl, 2011). Through descriptive statistics potential individual triggers can be detected.
- d) The **analysis function and physician report** analyses and visualizes the data entered into the app, including headache types, monthly headache occurrence, monthly average pain intensity and frequency of headaches, trigger statistics, headache distribution by time-of-day, day-of-week, and days-in-month and medication intake in weekly and monthly reports, as well as via the in-app calendar. This helps users to self-monitor the course of the disease and their medication intake. The report can be used to facilitate patient-physician communication.
- e) For the **personalized education about disease- and trigger management** the M-sense Migräne app includes 20 individualized knowledge lessons about migraine (e.g. symptoms, trigger factors and causes) and its treatment options (acute and preventive).

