## 7.2 Control group

The control group will gain access to the control study app, an app configuration of the M-sense Migräne app. The control study app will serve as a data input tool and, thus, only include features for study data collection such as a limited headache and medication intake diary and questionnaires. The control study app will serve as a documentation “black box” that will not provide any feedback or interventions about their data entries or behavior. E.g. the user will not be shown the result of headache attack classification

or descriptive statistics about headache patterns. Headache entries can only be seen retrospectively for one week. The documentation within the app assures that both groups have the same way to document outcomes and avoids possible bias by digital placebo effects.

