## 12.2 Data monitoring

M-sense Migräne's data validity is established as a CE marked medical device and reviewed regularly as part of its quality management system. An audit trail log covering the data trail from each participant's

data entry to the export will be reviewed by the study investigators. Further procedures to test data validity will be established by the investigators.

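### The seven-day limit on entering or editing diary data is stated only for the control app; unless it also applies to M-sense Migräne, the primary-endpoint diary differs by arm after randomisation

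*Combined protocol and SAP*

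**What the plan says.** SAP section 4 describes the two apps in consecutive paragraphs. The control paragraph says that "patients cannot enter or edit headache attacks or medication intakes that date back seven days or longer". The intervention paragraph lists features and gives no time limit.

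Protocol 7.2 describes the control app as offering "a limited headache and medication intake diary and questionnaires" and adds: "Headache entries can only be seen retrospectively for one week". Protocol 7.1 item a) says that the M-sense Migräne diary "allows a real time tracking of headache occurrences, including headache characteristics, attendant symptoms and experienced pain intensity levels". Item d) says that past data are shown, including "medication intake in weekly and monthly reports, as well as via the in-app calendar". No entry or edit window appears anywhere in 7.1.

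Two passages present in-app documentation as a protection against bias. Protocol 4.2: "We decided to document all outcomes within the app in both groups to reduce the bias". Protocol 7.2: "The documentation within the app assures that both groups have the same way to document outcomes".

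Under Protocol 10.2 all participants complete the 28-day baseline in the control app. SAP 6.1 derives the primary endpoint from the headache diary. Protocol 12.2 plans a review of "An audit trail log covering the data trail" from data entry to export.

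**The concern.** The primary endpoint is a count taken from patient-entered diary records in an open-label trial. If one arm can add or alter an attack from two or three weeks ago and the other cannot, the two arms' counts come from different measuring procedures. Baseline adjustment would not remove this. Baseline was recorded in the control app by everyone, so only the intervention arm changes diary version at randomisation.

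Blinded classification would not remove it either. The physician works from the raw diary data, so any change that the patient has made is already in what the physician sees.

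Headache days and medication days come from the same app diaries and would be affected in the same way.

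**Working it through.** **1. What is stated for each arm**

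| Diary property | Control app | M-sense Migräne app |
|---|---|---|
| Entry and edit of older records | Barred from seven days back (SAP 4) | Not stated (SAP 4, Protocol 7.1) |
| Display of past entries | One week (Protocol 7.2) | Weekly and monthly reports, calendar (Protocol 7.1 d) |
| Daily yes/no headache question | Present (SAP 6.1) | Present (SAP 6.1) |
| Used at baseline | By everyone (Protocol 10.2) | By no one |

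The difference in display is certain. The difference in entry and editing is likely, because the rule sits among the features that set the control app apart and that diary is called limited. It is not stated.

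**2. Direction, if the windows differ**

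- An attack added late can raise the intervention-arm count.
- An attack edited or deleted late can lower it.
- Under SAP 10.4.3 a headache day without enough detail to classify is counted as a migraine day in both groups. Detail supplied late can turn that day into tension-type or other headache and lower the count. A control patient past the limit could not do this.

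The paths oppose each other, so the net sign cannot be settled from the documents.

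**3. Length of exposure**

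No per-patient diary freeze is described. SAP 10.1 prepares the clean file about 14 weeks after the last randomisation, and Protocol 10.3 gives both arms the full app after week 12. If the full app has no limit and no cut-off is applied at extraction, early participants' records could stay open for months.

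**4. Scale**

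Inputs from SAP 7: reductions of 1.69 and 0.42 days, SD 4.20, two-sided alpha 0.05, power 80%, 173 per group, and a pilot mean of 3.94 days in the second four weeks.

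The plan's own figure first:

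- Difference: 1.69 − 0.42 = 1.27.
- Normal approximation: n = 2 × (1.960 + 0.842)² × 4.20² / 1.27² ≈ 171.7, so 172 per group.
- Exact t-test: 172.65, so 173 per group. The stated 173 reproduces, with power 80.1%.

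The documents give no rate of late change, so what follows is assumption.

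- Net 5% of 3.94: 0.05 × 3.94 = 0.197 days; 0.197 / 1.27 = 15.5%.
- Net 10% of 3.94: 0.10 × 3.94 = 0.394 days; 0.394 / 1.27 = 31.0%.

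The effect of a net shift b on the planned t-test (173 per group, SD 4.20) uses a standard error of 4.20 × √(2/173) = 0.452. Power is evaluated at a difference of 1.27 − b, and the rejection rate under no true effect at a difference of b:

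| Assumed net shift b (days) | Share of 1.27 | Power if b works against the app | Rejection rate with no true effect (b in either direction) |
|---|---|---|---|
| 0 | 0% | 80% | 5% |
| 0.10 | 8% | 73% | 5.6% |
| 0.25 | 20% | 62% | 8.6% |
| 0.50 | 39% | 40% | 19.7% |

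**The case against.** The strongest reply is that the documents are silent on the M-sense Migräne window, and silence does not show that the windows differ. Reports and a calendar show that past data can be viewed, not that they can be changed. A reader might infer from SAP section 4 that attacks can be changed late in one arm only. The documents do not say so, and the same limit may exist in both apps. This stands, and it is why the point is conditional.

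A reader might also infer that late entries can only raise intervention-arm counts, so that any bias would be conservative. The documents do not support that either, because SAP 10.4.3 opens a path in the other direction.

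The wording in Protocol 7.2 can be read as meaning only that both arms record within an app. The one-week view is disclosed just before it, and different feedback is part of the intervention. That reading is fair for display. It would not cover a different window for changing endpoint data.

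Safeguards exist: the same daily question in both apps, reminders to document, and blinded physician classification that is not the label the patient sees. They should reduce late documentation in both arms. They do not prevent or detect a patient's change to raw symptom data.

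The size is not evidence. The 5 to 10% is assumed and taken as a net shift, whereas opposing changes could cancel. The 3.94 comes from 19 pilot patients in their second four weeks of app use, not weeks 9 to 12. This stands too.

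**Conclusion.** The point holds in conditional form. An asymmetric entry and edit rule is stated for the diary that produces the primary endpoint, with no matching rule for the other arm. The claim of same-way documentation is therefore not supported as written. If the windows are equal, one sentence settles it. If they differ, a stated protection against bias fails from randomisation onwards, and neither baseline adjustment nor blinded classification repairs it.

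The direction is unknown and the size cannot be estimated from the documents. The illustration of 0.20 to 0.39 days (16 to 31% of 1.27) rests wholly on an assumed net rate and a small pilot. It shows only that a modest net rate would matter in a trial sized with no reserve for dropout.

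**What to change.** In SAP 6.1, apply one entry and edit cut-off to endpoint diary data in both arms, covering baseline and weeks 1 to 12. There are two routes:

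- set the seven-day limit in the study build of both apps; or
- if entry and edit time stamps are available, analyse each diary day in both arms as it stood seven days later. Protocol 12.2 does not say that the audit trail records edit times or earlier states of a record, so this must be confirmed first.

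If the common cut-off is not made the primary rule, prespecify it as a sensitivity analysis. Either way, state the window for both apps, reconcile SAP section 4 with Protocol 7.2, and report the number of later changes by arm.

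The time-stamp route costs a data filter if the log supports it. The app route is a configuration change to a CE-marked product, whose cost the documents do not give. The downside of both is that some genuine late intervention-arm entries are dropped, as they already are in control. If the windows already match, only the clarifying sentence is needed.
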